**Sample Size Considerations**

Presentation of sample size is based on achieving 80% power overall to demonstrate that improvement rate in *mindstreams score* is at least 12%. An improvement rate of at least 10% in the neurocognitive score in treatment group (compared to baseline, prior to HBOT treatment) would be an appropriate clinical target for HBOT treatment success and of sufficient interest to encourage further investigation of HBOT treatment for post TBI patients suffering chronic neurocognitive deficiencies.

Sample size is based on the assumption that exposure to the *mindstreams* tests at baseline without any additional training might induce 2% score improvement in the second test, following treatment, (test-retest effect). Assuming a true success rate of 12% a sample of N = 31 will provide 80% power to show that HBOT treatment induces at least 10% improvement on *neurocognitive test score*. This is based on a power analysis using the normal approximation for the binomial, with one-sided Alpha=0.05.

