**Inclusion criteria**

- An incident of mild traumatic brain injury 1-5 years prior to the inclusion in the study.
- All patients have to have complaints regarding persistent (stable not improving) neurocognitive deficiencies (memory, concentration, etc.) without noticeable improvement during the last month prior to their enrolment.
- Age 18 years or older.

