***End-point evaluation***

**Neurocognitive evaluation**

The neurocognitive evaluation will be done at baseline and after 2 months for all patients. In the cross group a 3^rd^ evaluation will be performed after 4 month- after crossing and completing 2 months of HBOT treatment. Cognitive function will be assessed using the one-hour Mindstreams Computerized Cognitive Test Battery (Mindstreams; NeuroTrax Corp., NY). Detailed description of the tests can be found on Neurotrax website ([www.neurotrax.com](http://www.neurotrax.com)).

To minimize differences in age and education, each outcome parameter will be normalized and fit to an IQ-like scale (mean=100, S.D=15) according to patient's age and education. Normalized subsets of outcome parameters will be aggregated to produce four index scores relevant to mild TBI: **Memory, Attention, Executive function,** and **Information Processing Speed**.

Three different test versions exist in the Mindstreams testing battery to allow repeated administrations, test-retest reliability for those versions were evaluated and found high, with no significant learning effect [[23](#_ENREF_23),[24](#_ENREF_24)].

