### Primary Efficacy Analysis

For the primary end point, Neurocognitive function (using Mindstreams neurocognitive battery test score), we will compute Overall Proportion of Success:

The following hypotheses are specified and will be tested separately:

For Neurocognitive *tests score* proportion of improvement:

H_0_: p_1=_ p _2_

H_1_: p_1>_ p_2_

While p1= Neurocognitive function (using Mindstreams neurocognitive battery *tests score*) improvement as a result of the HBOT training (assumed to be 0.12); and

p2= Neurocognitive function (using Mindstreams neurocognitive battery *tests score*) improvement as a result of test-retest effect (assumed to be 0.02)

This hypothesis will be tested by:

1. Constructing a one-sided, lower 95% confidence interval about the observed Overall Proportion of Success in the relevant cohort.
2. Examining whether the lower limit of the confidence interval is at or above the success criterion

Study success will be declared if the following is met:

1. Lower confidence limit of HBOT treatment success is at 0.12 or above

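### The improvement target is a percentage of baseline on a norm scale whose zero is arbitrary, so it has no fixed meaning and, if applied per patient, sets the lowest bar for the lowest scorers

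*Protocol*

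**What the plan says.** **Scale.** In the Neurocognitive evaluation section, "each outcome parameter will be normalized and fit to an IQ-like scale (mean=100, S.D=15) according to patient's age and education". The normalised parameters are then combined into four index scores. On retesting, the section says that "test-retest reliability for those versions were evaluated and found high, with no significant learning effect". It gives no reliability coefficient.

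**Target.** The Sample Size Considerations describe the clinical target as "An improvement rate of at least 10% in the neurocognitive score in treatment group (compared to baseline, prior to HBOT treatment". The practice effect uses the same unit: a first exposure "might induce 2% score improvement in the second test, following treatment, (test-retest effect".

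**Use in the calculation.** The same section then treats such figures as proportions: "Assuming a true success rate of 12% a sample of N = 31 will provide 80% power", by a normal approximation to the binomial. The Primary Efficacy Analysis section computes an overall success proportion in one cohort and asks whether its lower one-sided 95% confidence limit reaches 0.12. The comparison value p2 is "improvement as a result of test-retest effect (assumed to be 0.02".

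**Who enters.** The Inclusion criteria rest on complaints: "All patients have to have complaints regarding persistent (stable not improving) neurocognitive deficiencies". They set no limit on the test score, so a wide range of baseline values is eligible.

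**The concern.** On a norm scale the natural unit is the standard deviation. The zero is only a consequence of placing the norm mean at 100. Had the mean been set at 50 with the same SD, an identical gain would be a different percentage. A percentage of baseline is therefore not a stable measure of improvement, and the target does not say how large a gain is meant.

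If each patient is classed as improved or not against their own baseline, a second effect follows. The required gain is smallest for patients who start low. With imperfect reliability these are also the patients whose scores tend to rise on retest without treatment. Both push the same way, so the success proportion depends partly on the cohort's baseline mix. The success rule in the Primary Efficacy Analysis section sets one cohort against a fixed limit, so the control arm cannot absorb this drift.

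**Working it through.** **The plan's own figure.** N = 31 can be reproduced with a one-sample binomial normal approximation, p0 = 0.02 and p1 = 0.12:

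n = [(z_α·√(p0·q0) + z_β·√(p1·q1)) / (p1 − p0)]²

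- two-sided α = 0.05: n = 30.02, rounded up to 31
- one-sided α = 0.05, as stated: n = 25.4, rounded up to 26

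The alpha mismatch is a separate matter, and the present point does not rest on N. What the reproduction shows is that 12% and 2% enter as proportions of patients. That supports, without proving, a per-patient success rule.

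**Step 1: the bar in points (no assumption beyond a per-patient rule).** Required gain = 0.10 × baseline; in SD units, divide by 15.

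| Baseline | Gain needed | SD units |
|---|---|---|
| 70 | 7.0 | 0.47 |
| 85 | 8.5 | 0.57 |
| 100 | 10.0 | 0.67 |
| 115 | 11.5 | 0.77 |

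The bar at 115 is 11.5 / 7.0 = 1.64 times the bar at 70.

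**Step 2: chance success by baseline.** Assumptions, none of them in the protocol: patient mean 90, patient SD 15, retest correlation r = 0.8, bivariate normal scores, no treatment or practice effect. Given baseline b, follow-up has mean 90 + r(b − 90) and SD 15·√(1 − r²) = 9.0.

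- b = 70: expected follow-up 74. 10% rule: P(≥ 77) = 1 − Φ(3/9) = 37%. 10-point rule: P(≥ 80) = 1 − Φ(6/9) = 25%.
- b = 115: expected follow-up 110. 10% rule: P(≥ 126.5) = 1 − Φ(16.5/9) = 3.3%. 10-point rule: P(≥ 125) = 1 − Φ(15/9) = 4.8%.

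**Step 3: chance success overall.** For the 10% rule, Y − 1.1X has mean −0.1 × 90 = −9 and SD 15·√(2.21 − 2.2r). For a fixed bar, Y − X has mean 0 and SD 15·√(2 − 2r).

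| Rule | r = 0.8 | r = 0.9 |
|---|---|---|
| 10% of baseline | Φ(−9/10.06) = 18.6% | 10.5% |
| 9 points (10% of the assumed mean) | Φ(−9/9.49) = 17.1% | 9.0% |
| 10 points | Φ(−10/9.49) = 14.6% | 6.8% |

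The 9-point row is the fair comparison for the unit alone: it accounts for about 1.5 percentage points at either correlation. The further fall with 10 points comes from a harder bar.

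**Step 4: sensitivity.** At mean 90, chance success under the 10% rule at baseline 70 is 53%, 37% and 22% for r = 0.6, 0.8 and 0.9; at 115 it is 3.7%, 3.3% and 1.6%. Over means of 85 to 100 and r from 0.6 to 0.9, the overall rate under the 10% rule runs from 8% to 27%.

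**The case against.** The strongest reply is that the protocol never writes a per-patient rule. The 10% appears only as a clinical target in the sample-size section, and the only numeric criterion in the Primary Efficacy Analysis section is 0.12. If 10% means a change in the group mean, nobody is classed as improved and the rates in Steps 2 to 4 do not apply. This stands. It limits the point to the arbitrary zero under that reading, and makes the rest conditional on the binomial wording.

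Second, most of the chance success is regression to the mean, which affects any change criterion. This also stands: a 10-point rule still leaves 25% against 5%. The baselines shown are also towards the tails; under the assumed distribution about 9% of patients lie below 70 and 5% above 115.

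Third, a covariate list is commonly left to the SAP, which is not at hand. That is fair, so the absence of one is not held against the protocol. The unit of the target is fixed in the protocol itself.

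Three stronger readings are tempting, and the documents do not support them:

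- *That a 19% chance rate contradicts the assumed 2%.* The Sample Size Considerations describe the 2% as a score change from retesting, so it is not clearly a share of patients passing a threshold.
- *That the whole problem arises whether a mean or a proportion is analysed.* Only the arbitrary zero survives under a group-mean reading.
- *That chance baseline imbalance between arms is the main harm.* The stated success rule contains no arm comparison in which imbalance could act. Even supposing one, a 5-point imbalance (baseline means 87.5 and 92.5, r = 0.8, otherwise as in Step 2) shifts chance success by about 4.0 percentage points under the 10% rule and 2.4 under 10 points.

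**Conclusion.** The point holds in limited form. A target expressed as a percentage of baseline has no fixed meaning on a scale with mean 100 and SD 15. That follows from the protocol's text alone.

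If success is judged per patient, the bar runs from 0.47 SD at baseline 70 to 0.77 SD at 115, and steepens a gradient that regression to the mean already produces. With mean 90, SD 15, r = 0.8 and no effect, the contrast is 37% against 3%, rather than 25% against 5% with a 10-point bar. The effect of the unit on the overall rate is small: 19% against 17% for a matched 9-point bar. The patient mean, patient SD and correlation are assumptions.

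This is a minor-to-moderate issue. It does not by itself invalidate the trial, and it is best settled together with the question of whether 10%, 12% and 2% are score changes or proportions of patients.

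**What to change.** 1. In Sample Size Considerations and Primary Efficacy Analysis, express improvement in points or SD units of the normalised scale, the same for every patient. One example is 10 points (10/15 = 0.67 SD), which equals the stated 10% at the norm mean. Say explicitly whether it applies to each patient or to the group mean.
2. Restate the 12% and 2% assumptions on that definition and recheck the sample size against them.
3. Judge the treatment effect by comparing the randomised arms at 2 months, with baseline score as covariate. A fixed bar alone does not remove regression to the mean. The model details can sit in the SAP.

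**Cost.** No new data are needed, since both arms are already tested at baseline and 2 months. The work is rewording and a revised power calculation, which may change N. The familiar 10% figure is lost. With a 10-point bar, a patient at 70 would need 10 points instead of 7 to count, and a patient at 115 would need 10 instead of 11.5.

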**Randomization**

Since the diversity of the patients included in the study, after signing the informed consent is expected to be high, no stratifies criteria will be used. Patients will be randomized in 1:1 fashion to either treatment or controlled-cross group.

There will be no placebo in the cross group during the control period. The only way to give “placebo” of HBOT, is to bring the patients to the hyperbaric chamber and to increase the environmental pressure in a way the patients will “feel the hyperbaric pressure” in their ears. However, Henry’s law states: “the amount of a given gas dissolved in a given type and volume of liquid is directly proportional to the pressure of that gas in equilibrium with that liquid”. Thus, hyperbaric environment significantly increases the dissolved oxygen pressure even if a person holding his breath [[29](#_ENREF_29)]. Moreover, the alternative of hosting the patients in the hyperbaric chamber without any pressure increase cannot serve as a real placebo since the patients will not feel the pressure. Accordingly, the only real “placebo” could be achieved by increasing the pressure and reducing the percentages of the oxygen but that holds significant safety consideration.

From the ethical point of view, it is deemed unethical to “treat” the patients (40 sessions in the hyperbaric chamber) while they actually know that it is a placebo. In order to somewhat compensate for this limitation, the control will be a cross group and after the 2^nd^ evaluation at the end of a control period they will be crossed to HBOT. The cross for treatment enables intra-group efficacy evaluation in both treatment and control group.

Since the patients will know they are not receiving HBOT during the control period they will not be blinded with regard to the treatment arm. Accordingly, the quality of life evaluations will not be blinded. However, the complete blindness evaluation can be assured in both of the primary end points of this study, The Mindstreams computerized evaluation and the brain SPECT evaluation done by the radiologist.

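### The sample-size sentence is wrong as worded: with a true rate of 12%, N = 31 gives 7% to 12% power, not 80%, to show at least 10%

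*Protocol*

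**What the plan says.** Three statements in the protocol's Sample Size Considerations bear on this point.

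- The aim: "Presentation of sample size is based on achieving 80% power overall to demonstrate that improvement rate in" the Mindstreams score is 12% or more.
- The power claim: "Assuming a true success rate of 12% a sample of N = 31 will provide 80% power to show that HBOT treatment induces" an improvement of 10% or more in the neurocognitive score.
- The method: "This is based on a power analysis using the normal approximation for the binomial, with one-sided Alpha=0.05".

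Just before the power claim, the section assumes that repeat testing alone may raise the score by 2%.

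Primary Efficacy Analysis then sets H0: p1 = p2 against H1: p1 > p2. Here p1 is the improvement under HBOT (assumed 0.12) and p2 is the retest effect (assumed 0.02). The test is a one-sided lower 95% confidence limit on one observed proportion, and success is declared only if that limit reaches 0.12.

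The Randomization section says "Patients will be randomized in 1:1 fashion to either treatment or controlled-cross group". The protocol does not say whether 31 is the total, the number per arm or the number of evaluable treated patients.

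**The concern.** The power sentence fixes every input: truth 12%, value to be shown 10%, one-sided 0.05, 80% power, a named method and N = 31. A gap of two percentage points between proportions near 10% cannot be detected with 31 patients.

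The other figures do not settle what was meant. The text offers 10%, 12% and 2% as the value to be exceeded, and the success rule uses 12%, which is also the assumed truth.

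The stated 80% is what readers and the ethics committee rely on to judge whether the trial can answer its primary question. At present that figure is not tied to any one test.

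**Working it through.** **Inputs.** From Sample Size Considerations: N = 31, power 80%, one-sided alpha 0.05, true rate 0.12, target 0.10. From Primary Efficacy Analysis: p1 = 0.12, p2 = 0.02, success limit 0.12. No dropout rate is given, so none is applied.

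**Formulae for one group (normal approximation).**

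n = [z_a·√(p0·q0) + 0.842·√(p1·q1)]² / (p1 − p0)²

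power = Φ{[(p1 − p0)·√n − z_a·√(p0·q0)] / √(p1·q1)}

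z_a is 1.645 one-sided and 1.960 two-sided; √(0.12 × 0.88) = 0.325; √31 = 5.568.

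**1. The claim as worded: 0.10 against 0.12.** √(0.10 × 0.90) = 0.300.
- n = [(0.4935 + 0.2736) / 0.02]² ≈ 1,471.
- Power at 31 = Φ[(0.1114 − 0.4935) / 0.325] = Φ(−1.18) = 12.0%.
- Exact binomial: 7 or more of 31 are needed (size 0.031); power is 7.1%.

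The stated 31 and 80% are not reproduced. If the aim is instead to show more than 12% when the truth is 12%, power cannot exceed alpha at any N.

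**2. One group, 0.12 against a fixed 0.02.** √(0.02 × 0.98) = 0.140.
- One-sided 0.05: n = [(0.2303 + 0.2736) / 0.10]² = 25.4, so 26. Power at 31 = Φ[(0.5568 − 0.2303) / 0.325] = Φ(1.005) = 84%.
- Two-sided 0.05: n = [(0.2744 + 0.2736) / 0.10]² = 30.02, so 31, with 80.8% power. This is the only version tried that returns 31.
- Expected successes under the null are 31 × 0.02 = 0.62, too few for the approximation. Exactly, 3 or more of 31 are needed (size 0.024) and power is 73.6%. Power first reaches 80% at N = 35 (79.2% at 34, 80.8% at 35).
- One-sided variants of the approximation give 35 (continuity correction or arcsine) and 66 (Wald).

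**3. Two randomised arms, 0.12 against 0.02, one-sided 0.05.** The pooled rate is 0.07; √(2 × 0.07 × 0.93) = 0.3608; √(0.1056 + 0.0196) = 0.3538.
- n per arm = (1.645 × 0.3608 + 0.842 × 0.3538)² / 0.01 = 79.4, so 80.
- 31 per arm: Φ[(0.5568 − 0.5935) / 0.3538] = Φ(−0.10) = 46%.
- 31 in total (15.5 per arm, √15.5 = 3.937): Φ[(0.3937 − 0.5935) / 0.3538] = Φ(−0.56) = 29%.

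**4. The success rule: lower limit at or above 0.12.** With Clopper-Pearson limits at N = 31, at least 8 successes are needed. If the true rate is 0.12, P(X ≥ 8) = 2.7%. Wald limits give the same; Wilson limits need 7 and give 7.1%.

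| Test | Needed for 80% | Power at N = 31 |
|---|---|---|
| 10% vs 12%, one group (as worded) | about 1,471 | 12% normal, 7% exact |
| 2% vs 12%, one group | 26 normal, 35 exact | 84% normal, 74% exact |
| 2% vs 12%, two arms | 80 per arm | 46% (31 per arm), 29% (31 total) |
| Lower limit ≥ 12%, truth 12% | not attainable | 2.7% (Clopper-Pearson) |

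**The case against.** The strongest defence is that the 10% was never meant as a null value. The 2% retest effect comes directly before the 12% rate, and the hypotheses set 0.12 against 0.02, so 10% is plausibly the difference between them. On that reading the stated formula gives 84% power at 31, so N is slightly generous rather than short. The value 31 also follows at two-sided 0.05, which suggests an error of sidedness and wording rather than a trial planned at 7% power. Finally, the protocol defines p2 as an assumed retest constant and tests one proportion, so the two-arm powers belong to a test it does not specify.

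Much of this stands. A reader might infer that no reading of the protocol's figures reaches 80%. That is too strong, because the one-group test against 2% does so by the method named. The two-arm figures hold only if p1 and p2 are compared between arms. Nor would a negative result be uninterpretable: a confidence interval can be read whatever the planned power. Loss through the completer-only analysis set cannot be sized, because no dropout rate is given and 31 may already count evaluable patients.

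The defence does not rescue the sentence. It names 10% as the thing to be shown and a one-sided alpha. The approximation behind the 84% fails with 0.62 expected events. The success rule uses neither 2% nor 10%.

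**Conclusion.** The power statement is wrong as worded: 12% (normal) or 7% (exact) in place of 80%, with about 1,471 patients needed in place of 31. This rests only on the protocol's own inputs.

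The likeliest intention, one group at 12% against a fixed 2%, nominally exceeds 80% but has 74% exact power at 31. It returns 31 only at a two-sided alpha that the protocol does not use. A comparison between the arms would be well short of 80% whether 31 is per arm or the total. Under the stated success rule a true rate of 12% would succeed about 3% of the time (Clopper-Pearson).

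It would be going too far to say that the trial itself has 7% power: the protocol does not settle which test 31 was meant to serve. The paragraph and the success rule must be corrected together.

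**What to change.** 1. Delete the sentence that claims 80% power to show 10% or more from a true 12%.
2. State one contrast, one null value and one alpha with its sidedness. Say whether 31 is the total, per arm or evaluable treated patients.
3. Restate the power that this N gives for that test, by exact calculation if the endpoint stays binomial.
4. Change the success criterion in Primary Efficacy Analysis to the same null value. Otherwise the rewritten paragraph would still contradict it.

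If the sponsor prefers to compare mean Mindstreams score between HBOT and control, the SD, baseline mean and retest correlation must be declared as assumptions, with the range of power. For example, take a 10-point difference (12% minus 2% of an assumed mean of 100), the scale's normative SD of 15, a retest correlation r of 0.5 to 0.8 and baseline-adjusted analysis at one-sided 0.05. The residual SD is 15·√(1 − r²), that is 13.0 to 9.0. Power with 31 in total (16 and 15) is then about 67% to 91%. If these patients' baseline mean were 85, 10% would be 8.5 points and the range 55% to 82%. It cannot therefore be promised that this route needs no extra patients.

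The cost is a rewritten paragraph and an aligned success rule. The downside is that the stated power may become less favourable.

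### N = 31 does not follow from the protocol's stated inputs: at one-sided alpha 0.05 the named formula gives 26, and 31 patients have about 84% nominal power, not 80%

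*Protocol*

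**What the plan says.** Under Sample Size Considerations the protocol states: "Assuming a true success rate of 12% a sample of N = 31 will provide 80% power", the aim being "to show that HBOT treatment induces at least 10% improvement" on the neurocognitive score. On method it adds: "This is based on a power analysis using the normal approximation for the binomial, with one-sided Alpha=0.05".

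The Primary Efficacy Analysis gives the two rates. The null rate p2 is "improvement as a result of test-retest effect (assumed to be 0.02") and the alternative p1 is "improvement as a result of the HBOT training (assumed to be 0.12"). The test is carried out by "Constructing a one-sided, lower 95% confidence interval about the observed Overall Proportion of Success in the relevant cohort". Success is declared on this condition: "Lower confidence limit of HBOT treatment success is at 0.12 or above".

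The protocol thus fixes alpha, sidedness, power, both rates and the formula family, so N can be checked directly. It mentions neither an alpha of 0.025 nor an attrition allowance.

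**The concern.** When a protocol gives every input to a sample-size calculation, the reader should be able to recover N. Here that fails: the stated alpha, power, rates, method and N cannot all be right together. This statement is the protocol's only justification for its size, so a reader cannot tell what the trial was designed to deliver. The mismatch also raises the question of whether a different alpha was used for sizing than for the test, which would matter because alpha fixes the confidence limit that decides success.

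**Working it through.** **Inputs.** p0 = 0.02 and p1 = 0.12 (Primary Efficacy Analysis); power 80%, one-sided alpha 0.05, normal approximation for the binomial, N = 31 (Sample Size Considerations). I read N as the number of patients analysed in a one-sample test, because the stated test is a confidence limit about a single observed proportion.

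**Formula.** n = [(z_alpha·√(p0(1−p0)) + z_power·√(p1(1−p1))) / (p1−p0)]²

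with √(0.02·0.98) = 0.1400, √(0.12·0.88) = 0.3250, p1−p0 = 0.10 and z_0.80 = 0.8416.

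**Attempt to reproduce 31 at the stated alpha** (z = 1.6449):
- (1.6449·0.1400 + 0.8416·0.3250)/0.10 = (0.2303 + 0.2735)/0.10 = 5.038
- n = 5.038² = 25.38, so **26** (nominal power at 26: 80.5%)

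**Nominal power at 31, one-sided 0.05:**
- (0.10·√31 − 1.6449·0.1400)/0.3250 = (0.5568 − 0.2303)/0.3250 = 1.005, so power is **84.2%**

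**What does give 31:**
- One-sided alpha 0.025 (z = 1.9600): (0.2744 + 0.2735)/0.10 = 5.479; n = 30.02, so 31 (nominal power 80.8%).
- An attrition allowance on 26 (assumption; none is stated): 26/0.85 = 30.6 and 26/0.84 = 30.95, both rounding up to 31. At 10% the figure is 29, at 20% it is 33.

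**Other methods at one-sided 0.05 with 0.02 and 0.12:**

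| Method | n |
|---|---|
| Continuity-corrected | 35 |
| Arcsine | 35 |
| Exact binomial | 35 |
| Null variance only | 13 |
| Alternative variance only | 66 |
| Two-sample comparison | 80 per arm |

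None gives 31. If the 10% target were read as the null rate, testing 0.12 against 0.10 would need about 1,471.

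**How good the approximation is at n = 31, null 0.02.** Two or more successes has probability 12.7% under 0.02, which is too high; three or more has 2.4%. The exact test therefore needs 3 of 31, and its power at 0.12 is **73.6%**.

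**The written success rule at n = 31.** The one-sided lower 95% limit must reach 0.12. By Wald limits:
- 7/31: 0.2258 − 1.6449·√(0.2258·0.7742/31) = 0.102, which fails
- 8/31: 0.2581 − 1.6449·√(0.2581·0.7419/31) = 0.129, which passes

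Clopper-Pearson limits also need 8. The probability of 8 or more successes is 2.7% at a true rate of 0.12 and about 1 in 10 million at 0.02.

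**The case against.** The strongest reply is that the discrepancy is harmless. If 26 suffice and 31 are used, nominal power is higher than claimed, so the error is conservative, and the gap may simply be an allowance for patients lost from the primary efficacy set, which is restricted to completers without major protocol violations. The direction is as stated, on the nominal formula. But the text says that 31 provides 80% power, which presents 31 as the powered sample and not as an inflated enrolment target, and it states no allowance. The statement is still wrong as written.

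A reader might infer more: that the trial was really sized at one-sided 0.025 and then tested at 0.05, so that success is judged at twice the intended false-positive rate. The documents do not support this, for two reasons.
- That 0.025 was used is an inference from one numerical match. Attrition on 26 gives the same number, and so does a nominal power target of about 84%. Even an ill-fitting variant does (0.02 against 0.10, null variance only, continuity-corrected: 30.14, so 31), although it contradicts the stated 12%.
- Sample size does not set the type I error; the decision rule does. The sizing text and the confidence limit agree on one-sided 0.05, and under the written rule the chance of success at a true rate of 0.02 is practically nil.

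It may also seem that changing to 0.025 and a lower 97.5% limit would be a free repair. It is free only with exact limits against 0.02, where the boundary is 3 of 31 at both levels. Under the written 0.12 threshold the boundary moves from 8 to 9 of 31 and power at 0.12 falls from 2.7% to 0.9%. With a Wald limit against 0.02 it moves from 4 to 5, and power falls from 52% to 31%. The protocol does not name the type of interval.

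**Conclusion.** The sample-size statement is not reproducible from its own inputs. The named method gives 26, not 31, a gap of five patients; equivalently, nominal power at 31 is about 84%, not 80%. The cause cannot be determined from the protocol, and there is no inflation of the false-positive rate. Taken alone this is a reporting error of modest size.

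The conclusion rests on a one-sample test against 0.02 with 31 patients analysed. Within that setting the normal approximation is poor: with so few expected successes, exact power at 31 is 73.6%, below the 80% claimed. The nominal figures therefore need that caveat wherever they are quoted.

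No version of the calculation describes the success criterion as written. A lower limit at or above 0.12 places the threshold at the assumed true rate, so power there is 2.7%. That conflict is larger than the one in N, and restating N without addressing it would leave a coherent calculation for a test that the protocol does not perform.

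**What to change.** Keep one-sided alpha 0.05 and the one-sided lower 95% limit. In Sample Size Considerations, replace the N and power statement with text to this effect:

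*Against a null success rate of 0.02, with a true rate of 0.12, one-sided alpha 0.05 and the normal approximation for the binomial, 26 evaluable patients give 80% nominal power and 31 give about 84%. These figures are approximate: an exact test against 0.02 with 31 patients requires at least 3 successes and has 73.6% power at 0.12.*

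If 31 was meant to cover attrition, say instead that 26 evaluable patients are required and give the assumed percentage (about 15 to 16%) that takes 26 to 31. If another derivation was used, state it.

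Add that the figures apply only to a test against 0.02 and not to the 0.12 criterion in the Primary Efficacy Analysis. At the same time, reconcile that criterion with the null of 0.02 and the 10% target, so that sizing and decision rule refer to one threshold.

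Restating the figures costs a few lines of text, no patients and no change of error rate. Reconciling the threshold needs a decision by the sponsor, and N should be rechecked against whichever threshold is kept.

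### The sample size of 31 and its 80% power rest on a normal approximation that fails with 0.62 successes expected under the null; on an exact basis against 0.02 the power is about 74%

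*Protocol*

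**What the plan says.** Protocol, Sample Size Considerations: "Assuming a true success rate of 12% a sample of N = 31 will provide 80% power". The section names one distributional method as the basis, "a power analysis using the normal approximation for the binomial", "with one-sided Alpha=0.05".

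Protocol, Primary Efficacy Analysis: the null hypothesis is p1 = p2 and the alternative is p1 > p2. Here p1 is "improvement as a result of the HBOT training (assumed to be 0.12") and p2 is "improvement as a result of test-retest effect (assumed to be 0.02"). The test has two steps. The first is "Constructing a one-sided, lower 95% confidence interval about the observed Overall Proportion of Success in the relevant cohort". The second is "Examining whether the lower limit of the confidence interval is at or above the success criterion". The type of interval is not named. The section then sets the success criterion for the lower limit at 0.12, not at the null value 0.02.

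**The concern.** The normal approximation to a binomial count needs a reasonable number of expected events. Here fewer than one success is expected under the null and fewer than four under the alternative. The count is then strongly skewed and moves in large steps of probability, so a size or power read from a normal curve can be well off.

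Two things are at stake. First, the 80% power quoted to justify 31 patients may not be obtained by any test that holds the stated 5%. Second, if the limit is set against 0.02, as the hypotheses suggest, the usual candidate limits put the boundary at 2, 3 or 4 successes. The false-positive rate and the power then depend heavily on which limit is used.

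**Working it through.** **Inputs.** N = 31, power 80%, one-sided alpha 0.05 (Sample Size Considerations); p2 = 0.02 and p1 = 0.12 (Primary Efficacy Analysis). I take 0.02 and 0.12 as proportions of patients, 0.02 as a fixed null value, and 31 as the number analysed in the single cohort tested.

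**Step 1: the plan's own figure.** One-sample normal approximation:

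n = [(z_α √(p0 q0) + z_β √(p1 q1)) / (p1 − p0)]²

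With z_α = 1.645, z_β = 0.842, √(0.02 × 0.98) = 0.140 and √(0.12 × 0.88) = 0.325:

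n = [(0.2303 + 0.2735) / 0.10]² = 25.4, so 26.

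The stated inputs therefore do not reproduce 31; at N = 31 this approximation gives 84.2% power. With z_α = 1.960 (two-sided 0.05) it gives 30.02, so 31. That matches the number but not the stated sidedness.

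**Step 2: expected counts.** Null: 31 × 0.02 = 0.62. Alternative: 31 × 0.12 = 3.72. Under the null the probability of no success at all is 0.98³¹ = 53.5%.

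**Step 3: boundary for each lower limit against 0.02.** For each count x of 31, the one-sided 95% lower limit is:

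| x | Wald | Score (Wilson) | Exact (Clopper-Pearson) |
|---|---|---|---|
| 2 | below 0 | 0.0216 | 0.0116 |
| 3 | 0.0094 | 0.0393 | 0.0269 |
| 4 | 0.0300 | 0.0593 | 0.0453 |

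The first count whose limit reaches 0.02 is 2 (score), 3 (exact) and 4 (Wald).

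**Step 4: true size and power.** These are binomial tails with n = 31: size = P(X ≥ x | 0.02), power = P(X ≥ x | 0.12).

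| Limit | Success at | True size | Power at 0.12 |
|---|---|---|---|
| Score | ≥2 | 12.7% | 90.1% |
| Exact | ≥3 | 2.4% | 73.6% |
| Wald | ≥4 | 0.3% | 52.0% |

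No row combines a size of at most 5% with 80% power. The pattern is not peculiar to 31: for N from 28 to 33 the size with the score limit runs from 10.8% to 14.1%, and with the Wald limit from 0.2% to 0.4%.

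**Step 5: sample size on an exact basis.** The smallest N with exact size at most 5% and power at least 80% is 35, with success at ≥3 (size 3.25%, power 80.8%).

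**Step 6: the success rule as written, with the limit at 0.12 or above.** The score limit at 7 of 31 is 0.127. The Wald and exact limits at 7 are 0.102 and 0.111, and at 8 they are 0.129 and 0.135. So 7 successes are needed with the score limit and 8 with the other two.

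| Limit | Success at | P(success) at 0.02 | P(success) at 0.12 |
|---|---|---|---|
| Score | ≥7 | about 2 in a million | 7.1% |
| Wald, exact | ≥8 | about 1 in 10 million | 2.7% |

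**The case against.** **The approximation is named only for planning.** A reader might infer that the trial's test itself uses a normal limit. The protocol does not say so: the approximation belongs to the power analysis, and the Primary Efficacy Analysis names no interval type. An analysis plan, not at hand here, could fix an exact limit. This stands, and the missing interval type is not in itself the fault. It does not rescue the power figure, which the protocol states and attributes to the approximation.

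**The written rule uses 0.12.** A reader might also infer that 12.7% or 0.3% is the false-positive rate of the trial's decision rule, or that two or three successes could win or lose depending on the formula. Neither holds for the rule as written. Two or three successes fail it under every method, and at a true rate of 0.02 it is almost never met. The figures apply only if the limit is set against the null value that the same section gives. Against 0.12 the three methods differ by a single patient.

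**The 2% and 12% may not be proportions of patients.** The sample-size text speaks of a 2% score improvement, the battery gives continuous scores, and no per-patient definition of success is stated. On that reading there is no binomial count and this calculation does not apply. The ambiguity is real. However, the protocol's use of the binomial, a success rate and an overall proportion of success supports the reading taken here.

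**The conflict between 0.12 and 0.02 is the larger problem.** Agreed. It has to be settled in the same edit.

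**Conclusion.** The point holds in a limited form. With 0.62 successes expected under the null, the normal approximation is not a valid basis for the sample size. The stated pair of one-sided 5% alpha and 80% power at 31 patients is not delivered by the score, Wald or exact limit when tested against 0.02. The exact limit, which keeps the size below 5%, gives 73.6% power, a shortfall of about 6 percentage points. The score limit exceeds 80% power only at about two and a half times the stated alpha (12.7 / 5).

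This rests on 2% and 12% being proportions of patients, on 0.02 being a fixed null value, on 31 being the number analysed in the cohort tested, and on the limit being compared with 0.02. The documents do not support the further claim that the written criterion has an inflated or erratic false-positive rate. With the limit set at 0.12 its weakness is the opposite: a 3–7% chance of success at the very rate the trial assumes.

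**What to change.** In Sample Size Considerations, replace the normal approximation with the exact binomial distribution. Then either restate the power at 31 analysed patients as about 74% for 0.12 against 0.02, or raise the number analysed to 35 to keep 80%.

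In Primary Efficacy Analysis, name the Clopper-Pearson one-sided 95% lower limit. In the same edit, reconcile the 0.12 success criterion with the null hypothesis (p2 = 0.02), so that only one boundary is stated, with its true size and power. If 0.02 is the reference and 31 are analysed, that boundary is at least 3 successes, with size 2.4% and power 73.6%. Adding this boundary while leaving the 0.12 criterion in place would give the protocol two incompatible success rules: 3 of 31 is 9.7%, below 0.12 even as a point estimate.

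Cost: keeping 31 changes only the text but makes the stated power less favourable. Keeping 80% power takes four more analysed patients (35 − 31).
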